### Discontinuation criteria

Analyses will follow intention-to-treat (ITT) principles as far as possible. Therefore we will include in the analyses all schools and children initially randomised who provide data at baseline, including them for the purpose of analysis in the group originally allocated to them. To maximise the power of such analyses all reasonable and ethical steps will be taken to ensure the completeness of follow-up measures. Where data are missing we will use multiple imputation based on baseline data to replace missing data [20]. Children missing at baseline but present at one or more subsequent data collection time points will be treated as ‘other participants’ and excluded from the intention-to-treat analyses.

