### Schools withdrawal

If a school wishes to withdraw from the study we will attempt to collect data on the reasons for withdrawal. We will explore with the school the possibility of using all data collected up until that point and the possibility of still collecting data from pupils at the school at the final time point in order to maximise the chance of having more complete data on our key outcome measures (an ITT principle). Provided data is available from baseline, multiple imputation will be used to replace missing data. Where no baseline data are available all data will be excluded from analyses as there will be insufficient data to appropriately perform any multiple imputation of missing values.

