### Child withdrawal

Parents will have the opportunity to have their child not included in the study before commencement. Parents will also have the opportunity to withdraw their child from the study at any time point by informing the school. Further data will not be collected from children withdrawn from the study (missing data will be replaced based on multiple imputation from available data). As data will be collected anonymously, it will not be possible to withdraw data already collected. Children withdrawn from the study may not be left out of any whole class activities that form part of the intervention as to do so might involve taking the child out of the class whilst these activities were occurring.

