### Data collection methods

The primary outcome measure is smoking initiation based on objective measures at 48 months. A secondary measure will be self-reported smoking. These measures will also be assessed at baseline and at 12, 24, and 36 months post-baseline in order to explore the time periods over which the intervention might be best targeted. These data collection sessions will be completed in classroom time by the researchers and take approximately 30 minutes. Self-reported smoking and measures of cognitions (e.g. attitudes to smoking, intentions to resist smoking, self-efficacy over resisting, family smoking and friends smoking) will be collected via questionnaire completed individually but in a classroom setting. An objective measure of smoking will be completed individually outside a classroom setting. A number of measures of objective smoking are feasible. The two most common measures are breath carbon monoxide measures and saliva cotinine measures. Although saliva cotinine may be more effective in detecting occasional smoking (due to the greater half-life of 16–18 hours versus 4–6 hours in breath carbon monoxide) it also has a number of disadvantages. These include lower acceptability to adolescents, greater cost, and loss of ability to feed back the results to participants immediately. For this reason our objective measure of smoking will be obtained from breath carbon monoxide monitors (Micro+ Smokerlyzer® CO Monitor, Bedfont Scientific Limited, Kent, England). This instrument gives a measure of carbon monoxide in the breath in parts per million (ppm) accurate to within 2% based upon exhaling one breath into the device and has been adapted for use in adolescent samples. Although a number of factors influence carbon monoxide in the breath, recent smoking should significantly elevate levels. Carbon monoxide in the breath can be used as a reliable and valid measure of exposure to cigarette smoking [24], comparable in accuracy to blood carboxyhaemoglobin levels [25]. The Bedfont devices have been demonstrated to give reliable and valid assessments of smoking status [26] and have been employed by various researchers with adolescent samples [8,27]. Our secondary outcome measure, self-reported smoking, will be assessed by standard measures (as used in national surveys and our previous research; [8,28]).

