### Analyses

#### Analyses of primary and secondary outcome measures

The study uses a two group experimental design with schools of adolescents (all aged 11–12 years at outset) randomly allocated to one of two conditions: a repeated implementation intention condition targeting smoking or a control condition. The primary outcome will be objectively assessed smoking and the secondary outcome measure will be self-reported smoking. A two-level logistic regression will be used to model smoking outcomes at 48 months. Given that drop outs are expected, multiple imputation, based on regression methods, will be undertaken to ‘complete’ the data and ensure efficient analysis. This will be done for all participants for whom baseline data is available (to provide meaningful imputations) and will take into consideration the two-level hierarchical nature of the data. With this approach the results will be unbiased given the general assumption of missing at random (MAR) rather than the more restrictive assumption of missing completely at random (MCAR). Results from the multiple imputations will be combined using Rubin’s rules.

Subgroup analyses will be used to examine any differences between high and low deprived schools, between regions (West Yorkshire versus Staffordshire), and between boys and girls. We will use mediation analyses to explore the extent to which any intervention effects are mediated by changes in the measured cognitions as tested in our previous work (e.g., attitudes to smoking, intentions to resist smoking, self-efficacy to not smoke, etc.; [31-34]).

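### The protocol gives two different bases for the multiple imputation, and the general one, as worded, leaves out the smoking measured at 12, 24 and 36 months

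*Protocol article*

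**What the plan says.** Four sections of the protocol article bear on the imputation.

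- Discontinuation criteria, in the intention-to-treat paragraph: "Where data are missing we will use multiple imputation based on baseline data to replace missing data". This is the only general statement of what the imputation is built from.
- Child withdrawal: "missing data will be replaced based on multiple imputation from available data". For a child withdrawn after the first follow-up, this would take in post-baseline smoking.
- Schools withdrawal: "Provided data is available from baseline, multiple imputation will be used to replace missing data". Here baseline data are a condition for being imputed. The same section also raises with the school "the possibility of using all data collected up until that point".
- Analyses of primary and secondary outcome measures: "This will be done for all participants for whom baseline data is available (to provide meaningful imputations"). Again this is a condition of entry. The method is regression-based and two-level, with Rubin's rules, and no predictors are listed. The section adds: "With this approach the results will be unbiased given the general assumption of missing at random (MAR").

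On what is collected, Data collection methods says "The primary outcome measure is smoking initiation based on objective measures at 48 months", with self-report as the secondary measure. Of both it says: "These measures will also be assessed at baseline and at 12, 24, and 36 months post-baseline". The Abstract confirms that both are also taken at 48 months.

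**The concern.** Missing at random is always conditional on the variables in the imputation model. The Background gives regular smoking as 0.5% at age 11 and 15% at age 15, so nearly all of the smoking that the primary outcome counts begins after baseline. A pupil who starts smoking in the middle years and is absent at 48 months would, under a model built from baseline data, be imputed at roughly the average risk for his or her baseline profile. If smoking makes absence more likely, such a model cannot correct for it. A model containing the 12, 24 and 36 month measures can correct for the part that those measures capture.

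The Randomisation section expects 15% loss by age 15–16, so the imputed share is not trivial. At stake are the rate in each arm, the risk difference (which feeds the cost per non-initiation in the Economic analyses) and, if dropout among smokers differs by arm, the odds ratio from the primary logistic model. In addition, two written bases for the imputation leave a choice open after the data are seen.

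**Working it through.** **1. The plan's own figures.** Proposed sample size gives 0.85 × 18 × 120 = 1836 per arm. With m = 0.85 × 120 = 102 and ICC 0.01, the design effect is 1 + 101 × 0.01 = 2.01, and 1836/2.01 = 913. For 14% against 9%, two-sided alpha 0.05, a normal-approximation test with continuity correction has power 90.65%, as stated (91.8% without the correction). The odds ratio is (0.09/0.91)/(0.14/0.86) = 0.608, which matches the stated 0.61.

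**2. Inputs for the illustration.** From the protocol: true 48-month rates of 14% (control) and 9% (intervention), and about 15% loss. Assumed, because the protocol gives no such figures:
- smoking at 36 months is s = 10% in control and 6.4% in intervention;
- 70% of 36-month smokers smoke at 48 months;
- dropout depends only on 36-month smoking, at dS among smokers and dN among others;
- baseline data carry no information within an arm, which is the extreme case.

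**3. Formulae.** With P the true rate in the arm, the 48-month rate among 36-month non-smokers is b = (P − 0.7s)/(1 − s). Control: (0.14 − 0.07)/0.90 = 0.0778. Intervention: (0.09 − 0.0448)/0.936 = 0.0483. When baseline is uninformative, the imputed rate equals the rate among completers:

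R = [s(1 − dS)0.7 + (1 − s)(1 − dN)b] / [s(1 − dS) + (1 − s)(1 − dN)]

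**4. Equal dropout pattern in both arms, dS = 40%.** For 15% overall loss in control, dN = (0.15 − 0.1 × 0.40)/0.90 = 12.2%. The same dS and dN in the intervention arm give 14% loss there.
- Control: 0.1034/0.8500 = 12.2%.
- Intervention: 0.0666/0.8600 = 7.7%.
- Difference: 4.4 points instead of 5.0. Odds ratio: 0.605 against 0.608.

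With dS = 50% (dN = 11.1%) the rates are 11.4% and 7.2%, the difference is 4.2 points, and the odds ratio is still 0.605.

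**5. No true effect, dropout pattern differs by arm.** Both arms have a true rate of 14%, s = 10% and 15% overall loss.
- dS = 50%, dN = 11.1%: 0.0972/0.85 = 11.4%.
- dS = 20%, dN = 14.4%: 0.1159/0.85 = 13.6%.
- Spurious difference: 2.2 points, odds ratio about 0.82. It favours whichever arm loses more of its smokers.

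**6. A second set of assumptions, as a range.** Here s is 0.7 times the final rate in each arm, persistence is 70%, and loss is 15% in each arm.

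| Smokers' dropout relative to others | Intervention | Control | Odds ratio |
|---|---|---|---|
| Same in both arms | 9.0% | 14.0% | 0.608 |
| Twice, both arms | 8.4% | 13.1% | 0.604 |
| Three times, both arms | 7.8% | 12.4% | 0.598 |
| Twice, control only | 9.0% | 13.1% | 0.655 |
| Three times, control only | 9.0% | 12.4% | 0.700 |
| Twice, intervention only | 8.4% | 14.0% | 0.561 |
| Three times, intervention only | 7.8% | 14.0% | 0.519 |

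**7. With 36-month smoking in the model.** The rates are recovered under the same mechanism: 0.10 × 0.7 + 0.90 × 0.0778 = 14.0%, and 0.064 × 0.7 + 0.936 × 0.0483 = 9.0%.

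**The case against.** The strongest reply is that baseline data merely decide who can be imputed. Schools withdrawal and the Analyses section use them that way, and the sentence after the general statement deals with children who have no baseline data. The predictor list would normally sit in the analysis plan, which is not shown. Both points carry weight. A reader might infer that the trial will impute from baseline only and ignore the interim smoking data. The protocol does not say so: neither word appears, and Child withdrawal points to a wider set. The absence of a predictor list is no finding either. What stands is that the one general statement names a basis, and it disagrees with another section.

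A reader might also infer that the claim of unbiased results is wrong or not credible. The sentence is expressly conditional on missing at random, so it is correct as a conditional statement. The protocol also plans more than one visit day, a statistical exploration of dropout bias and adherence to HTA missing-data guidance. Baseline attitudes, intentions, self-efficacy and family and friends' smoking add some information, and the 0.5% concerns regular smoking only. These points soften the concern. They do not settle which variables the assumption is conditional on.

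Finally, a reader might infer that smoking-related dropout attenuates the treatment effect. On the planned logistic scale it hardly does so when the pattern is equal across arms; only the risk difference shrinks. Differential loss of smokers is conceivable, since schools know their allocation before letters go to parents and intervention pupils repeatedly endorse a plan not to smoke. Nothing in the protocol documents it.

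**Conclusion.** The concern holds as an inconsistency with a practical consequence. The protocol names two bases for the imputation. The general one, as worded, omits the collected variables that are likely to be the best predictors of the outcome and probably of dropout. Missing at random given baseline alone is a stronger assumption than the data require.

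Under the assumed inputs, with a dropout pattern equal across arms, the risk difference falls from 5.0 to between 4.2 and 4.4 points and the odds ratio stays within 0.01 of 0.608. With smoker dropout two to three times that of others in one arm only, the odds ratio runs from about 0.52 to 0.70. With no true effect, 50% against 20% smoker dropout gives about 2 points of spurious difference. All of this rests on assumed interim smoking, persistence and dropout, and on uninformative baseline data, so the figures show direction and plausible size and are not forecasts. Severity is moderate: it should be settled before 48-month data are seen, but it does not invalidate the design.

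**What to change.** Reconcile Discontinuation criteria with Child withdrawal, and align Schools withdrawal and the Analyses section, so that the two roles are separate:

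- **Who is imputed:** participants with baseline data, as now.
- **What the model contains:** arm, school (the two-level structure is already promised), baseline covariates, observed CO and self-reported smoking at 12, 24 and 36 months, and 48-month self-report where observed. The last is useful because CO is taken individually outside the classroom and self-report by classroom questionnaire, so a pupil may have one without the other.
- **The assumption:** in the Analyses section, state that missing at random, and hence the unbiasedness, is conditional on that set.

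Imputing separately by arm is optional. All the variables are already collected, so the cost is a few sentences and a slightly larger imputation model.

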### Schools withdrawal

If a school wishes to withdraw from the study we will attempt to collect data on the reasons for withdrawal. We will explore with the school the possibility of using all data collected up until that point and the possibility of still collecting data from pupils at the school at the final time point in order to maximise the chance of having more complete data on our key outcome measures (an ITT principle). Provided data is available from baseline, multiple imputation will be used to replace missing data. Where no baseline data are available all data will be excluded from analyses as there will be insufficient data to appropriately perform any multiple imputation of missing values.

### Child withdrawal

Parents will have the opportunity to have their child not included in the study before commencement. Parents will also have the opportunity to withdraw their child from the study at any time point by informing the school. Further data will not be collected from children withdrawn from the study (missing data will be replaced based on multiple imputation from available data). As data will be collected anonymously, it will not be possible to withdraw data already collected. Children withdrawn from the study may not be left out of any whole class activities that form part of the intervention as to do so might involve taking the child out of the class whilst these activities were occurring.

### Interim analysis and stopping rules

Overall smoking rates in the two conditions will be computed and presented to the Independent Trial Steering Committee (TSC; and associated data monitoring committee) each year. Evidence of considerably higher rates of smoking initiation in the intervention condition compared to the control condition could be considered by the Committee as reason to stop the trial. All adverse events would also be reported to the TSC.

### Randomisation

The unit of randomisation will be schools and our sample size calculations and analyses takes account of this clustering of the data. We believe randomising by school before the intervention begins is most appropriate in order to reduce the likelihood of contamination between the intervention and control conditions (randomising by individual or classroom risks such contamination). The Trial Statistician (RW) will use a random number generator to randomly allocate schools to the control or intervention arms of the trial. Schools have requested feedback on which condition they are randomised to before giving final agreement to participate and agreeing to send out letters to parents. The trial will therefore deviate from best practice in recruiting children to the trial after rather than before randomisation. We will monitor any consequential effects on participation rates. As we hope to recruit all classes in a school year movement between classes within a school should not be a problem. However, adolescents moving school during the RCT are likely to have missing data. Of those initially participating in the study at age 11–12 years we anticipate a cumulative loss to follow-up at age 15–16 years of 15% (based on our previous research, [8]). We will make efforts to minimize drop out (e.g., attempting to ensure each school is visited on more than one day to collect smoking measures) and any potential biases attributable to drop out will be explored statistically.

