Using these assumptions we have estimated that we require a total of 36 schools with 18 randomly allocated to the intervention arm and 18 to the control arm of the RCT. Within each school, we estimate that we need to approach at least 120 adolescents at baseline (approximately 4 classes per school). Based on an 85% recruitment rate (due to refusal to participate and non-attendance on testing days) the overall number of adolescents available for analysis will be: 0.85 * 18 * 120 = 1836 per group. The effective number of adolescents per group will be reduced further due to a design effect (i.e., adolescents clustered by school): Design effect = 1 + (m – 1)*ICC, where m is the number of participants per cluster. This yields a design effect of 2.01 and reduces the effective sample size per group to 913 (1836/2.01). This effective sample size yields a statistical power of 90.65% to detect a 5% difference in smoking initiation between the intervention (9% initiation) and control (14% initiation) arms using a two-sided test with an alpha of 0.05. Adding our correction factor for potential imbalances in recruitment would still provide a power of almost 90%. Therefore our proposed sample size is 4320 adolescents from 36 schools (18 intervention; 18 control), with approximately 120 adolescents being approached per school.

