### Intervention

This will be a phase III pragmatic randomised controlled trial conducted in two geographically distinct regions of England (West Yorkshire and Staffordshire) that will provide the information on which to base a decision about roll out of the intervention. The intervention involves asking adolescents to read simple anti-smoking messages and then to form an implementation intention by planning how, where, and when to resist smoking (i.e., refuse the offer of a cigarette). This intervention will be repeated every six months over a period of four years between the ages of 11–12 and 15–16 years (8 occasions; see flow chart of study procedures in Figure 1). The anti-smoking messages focus on simple-to-understand negative consequences of starting smoking and the positive consequences of remaining a never-smoker. The implementation inten-tion intervention is designed to give adolescents simple responses for how to refuse a cigarette and to link them to situations where a cigarette might be offered. Five options will be provided for *how* they could refuse the offer of a cigarette or resist the temptation to smoke (e.g., ‘No thanks, I don’t want to smoke; No thanks, I don’t want the habit; No cancer sticks for me; No thanks, smoking makes you smell bad; No, it’s bad for your health’; see [8]). Participants are required to check the options they plan to use or to write in an additional response. Similarly participants will be required to check *where* they would not smoke (e.g., ‘I will not smoke at school; I will not smoke at home; I will not smoke at a party; I will not smoke with my friends; I will not smoke if offered a cigarette’) and *when* they would not smoke (e.g., ‘I think I can make sure I don’t smoke this term’) and signal agreement with their plan not to smoke by ticking a box. The implementation intention will be presented as a paper and pencil questionnaire that adolescents read and complete in classroom time. Previous evidence has suggested that implementation intentions are more effective among individuals who are motivated to perform the behaviour [17]. Therefore combining the implementation intention with motivational messages is likely to be more effective than using implementation intentions alone. This was the combination used in our previous research [8,12]. The research has broadly followed the MRC framework for developing and evaluating complex interventions to improve health [29,30]. The pre-clinical through phases II testing of this repeated implementation intention intervention have been completed as part of this previous work. In particular, significant work has been completed to develop the intervention and test its feasibility and acceptability in appropriate samples of schoolchildren (see [12]). In the control condition participants will read persuasive messages encouraging them to complete all their home work and they will form an implementation intention in relation to completing all their homework.

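### The 36 schools are allocated with no stated stratification or constraint on region or school deprivation, although both can be known beforehand and both are planned subgroup factors

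*Protocol article*

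**What the plan says.** The Randomisation section of the protocol article makes the school the unit of randomisation and explains why. On method, it says only that the trial statistician "will use a random number generator to randomly allocate schools to the control or intervention arms of the trial". Neither that section nor any other visible text mentions stratification, blocking, minimisation or a balance constraint.

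The numbers per arm are set under Proposed sample size: "we require a total of 36 schools with 18 randomly allocated to the intervention arm and 18 to the control arm of the RCT".

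The Intervention section describes a trial "conducted in two geographically distinct regions of England (West Yorkshire and Staffordshire"). Under Analyses of primary and secondary outcome measures the article states: "Subgroup analyses will be used to examine any differences between high and low deprived schools, between regions (West Yorkshire versus Staffordshire"). Sex is the third subgroup factor. The primary model is given in one sentence, "A two-level logistic regression will be used to model smoking outcomes at 48 months", without a list of covariates.

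The allowance for imbalance under Proposed sample size (at most 1% of power) covers recruitment and dropout. It does not cover which kinds of school fall in which arm.

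**The concern.** Thirty-six is a small number of units to randomise. Region and school deprivation are school-level characteristics that can be established before allocation. The protocol regards both as important enough to define subgroups, yet the allocation as described makes no use of them. A draw of 18 schools from 36 balances such factors only on average, and a single draw can leave one arm with clearly more deprived schools or more schools from one region.

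Three things are at stake: the precision of the primary comparison, the comparability of the arms as a reader of the results will see them, and the strength of the two school-level subgroup analyses. Imbalance puts few schools in one arm of a subgroup. The analysis can adjust for these factors later, but it cannot restore balance once schools are allocated.

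**Working it through.** **1. The plan's own power figure.** Inputs from Proposed sample size: 120 pupils per school, 85% available, 18 schools per arm, ICC 0.01, 9% v 14%, two-sided alpha 0.05.
- Pupils per school: 0.85 × 120 = 102.
- Design effect: 1 + (102 − 1) × 0.01 = 2.01.
- Effective number per arm: 1836 / 2.01 = 913.
- Two-proportion test with continuity correction, mean rate 0.115: standard error under the null √(2 × 0.115 × 0.885 / 913) = 0.01493; under the alternative √((0.09 × 0.91 + 0.14 × 0.86) / 913) = 0.01489; correction 1/913 = 0.00110.
- z = (0.05 − 0.00110 − 1.96 × 0.01493) / 0.01489 = 1.32, so power is 90.65%. This matches the stated figure (91.8% without the correction).

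**2. Chance imbalance with 18:18 held.** If 18 of 36 schools are drawn at random, the number from a stratum of R schools in one arm is hypergeometric (36, R, 18). The article does not give the number of schools per region or per deprivation level, so R is assumed.

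| R (assumed) | Event | Probability |
|---|---|---|
| 18 | 12:6 or worse | 9.4% |
| 12 | 8:4 or worse | 28.9% |
| 9 | 6:3 or worse | 44.3% |

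Each event means at least two thirds of the stratum in one arm. With two independent half-and-half factors, the chance that at least one splits 12:6 or worse is about 18% (simulation).

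**3. What such an imbalance costs.** For a stratum split a:b with 18 schools per arm, the squared correlation between arm and factor is (a − b)² / [R(36 − R)]. In a linear approximation with equal school sizes, adjusting for the factor multiplies the variance of the arm effect by 1 / (1 − that value), relative to perfect balance.
- 12:6, R = 18: 36/324 = 0.111, factor 1.125.
- 8:4, R = 12: 16/288 = 0.056, factor 1.059.
- 6:3, R = 9: 9/243 = 0.037, factor 1.038.

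Within the stratum itself, the variance of the arm difference is proportional to 1/a + 1/b.
- 12:6 against 9:9: 0.250 / 0.222 = 1.125.
- 8:4 against 6:6: 0.375 / 0.333 = 1.125.
- 6:3 against 5:4: 0.500 / 0.450 = 1.11.

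**4. What using the factors would gain.** Suppose region and deprivation explain a share f of the between-school variance (assumed; the article gives no figure). The design effect becomes about 1 + 101 × 0.01 × (1 − f), with power calculated as in step 1.

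| f | Design effect | Effective n per arm | Power |
|---|---|---|---|
| 0 | 2.01 | 913 | 90.65% |
| 10% | 1.909 | 962 | 92.1% |
| 25% | 1.7575 | 1045 | 94.0% |
| 50% | 1.505 | 1220 | 96.8% |

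Most of this gain comes from including the factors in the model. Balanced allocation mainly avoids the losses in step 3.

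**The case against.** The strongest reply is that a random number generator is a source of randomness, not an allocation scheme. It can just as well be used to draw 18 of 36 schools or to produce stratified lists. The article is condensed and its randomisation flow chart is not visible, so a restriction may exist elsewhere. This stands as a caution: the point rests on what the Randomisation section describes. But that section covers the unit, its rationale, who allocates, the tool and even a departure from best practice, and it gives no restriction.

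A reader might go further and infer that allocation is a coin toss per school, which would leave the 18:18 split to chance. The text does not support that, because Proposed sample size states 18 schools per arm. Even under a coin toss, average power would be 89.8% against 90.65%, a loss of about 0.9 points.

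Two other strong readings also fail.
- Chance imbalance might be called confounding of the intervention effect. It is not bias in a randomised comparison, and the two-level model carries between-school variation in its standard error.
- An ICC of 0.01 implies a between-school SD of √(0.01 × 0.115 × 0.885) = 3.2 points, hence an SD of 3.2 × √(2/18) = 1.06 points in the arm difference, or about ±2.1 points at 95%. Setting this against the 5-point target as an extra harm would count it twice, since it is already inside the design effect of 2.01.

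It is also fair to say that subgroup analyses are valid without stratification, and that a covariate list may properly sit in an analysis plan. The allocation scheme cannot wait for that plan.

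**Conclusion.** The concern holds as a cheap and worthwhile improvement, not as an error that invalidates the trial. As described, the allocation does nothing to secure balance on region or deprivation. With 18:18 held, marked imbalance on one such factor has a probability of about 9% to 44% for strata of 18 down to 9 schools. The strata most likely to be unbalanced cost the primary comparison least. At the splits shown, the variance of the adjusted effect rises by about 4% to 12.5%, and that of the within-stratum effect by about 11% to 12.5%. More extreme splits cost more.

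The power gain of roughly 1.5 to 6 points depends wholly on the assumed 10% to 50% of between-school variance explained, and it comes mostly from adjustment. Even the low end would help, because the article's own imbalance correction takes power to just under the 90% it seeks. Stratum sizes and variance shares are assumptions throughout.

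**What to change.** Allocate schools by stratified randomisation within region × deprivation (for example above or below the median of a published school deprivation indicator), or by covariate-constrained randomisation on the same two factors, constrained to 1:1 overall. State the scheme in the Randomisation section, including how 18 per arm is secured. Include region and deprivation as fixed effects in the two-level logistic model. If a restriction is already in place, one sentence there settles the allocation part.

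The cost is small. Deprivation data must be in hand before allocation, and the model spends a few degrees of freedom. An exact 18:18 may still drift by a school or so, because strata can be odd in size, the target is at least 36 schools, and schools learn their arm before giving final agreement.
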